| Visit schedule and evaluation | Screening & washout period: ~14 days (Day -14 to Day 1 [Week -2 to 0]).  Treatment and F/U period: 12 weeks (Day 1 to Day 84 [Week 12]).  **Visit Schedule for Evaluation**  Visit 1: screening & washout, Day -14 to Day 1.  Visit 2: randomization, Day 1.  Visit 3: end of study, Day 84±7 from date of randomization.  **Schedule for Evaluation**  **1) Safety and tolerability evaluation**  Adverse events, physical examination, vital signs, laboratory tests (hematological test, blood chemistry), co-administered drugs.  Adverse events: V1-V3, at every visit.  Co-administered drugs: V1-V3, at every visit.  Vital signs (VS): at V1 and V3.  Physical examination: at V1 and V3.  Laboratory tests:  - Hematological test: at V1 and V3.  - Blood chemistry: at V1 and V3. |
| Inclusion criteria | 1. Subjects of Korean nationality who voluntarily decide to participate in the study after receiving and understanding a detailed explanation of the study and provide written consent. 2. Men and women who are ≥50 years old at the time of consent. 3. Persons who are available for follow-up for the duration of the study and who are able to perform tasks for the study, such as reading and filling out EQ-5D and VAS surveys. 4. Persons with a confirmed medical history of physically symptomatic osteoarthritis who score ≥40 mm on pain VAS performed at V2. 5. Persons deemed appropriate for the study based on the screening results (N.B.: subjects can be included at the discretion of the investigator even if laboratory test results are outside reference ranges). |

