## Drugs or therapies contraindicated prior to study participation

Subjects who received the following medications for the periods listed below cannot participate in the study:

1. NSAIDs (LDA [≤325 mg / day low dose aspirin] excluded) within 7 days prior to administration of the investigational product.
2. Gastroprotective agents (including H2 blockers, PPIs, misoprostol, etc.) within 7 days prior to administration of the investigational product.
3. IV or oral corticosteroids (oral corticosteroids corresponding to ≤7.5 mg / day prednisone, topical ointments, eyedrops, and nasal agents are excluded) within 7 days prior to investigational product administration.
4. Intraarticular or intramuscular corticosteroids or hyaluronic acid within 8 weeks prior to administration of the investigational product.
5. Glucosamine and / or chondroitin sulfate within 7 days prior to administration of the investigational product.
6. Lithium within 7 days prior to administration of the investigational product.
7. Antiretrovirals (atazanavir, atazanavir sulfate) within 7 days prior to administration of the investigational product.

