#### General precautions

1. Carefully consider the potential benefits and risks of this drug and other treatment options before deciding to use it. Since cardiovascular risk increases with increasing dosage and exposure to this drug, use the lowest effective dose for the shortest duration possible. In osteoarthritis patients, in particular, reassess regularly.
2. Gastrointestinal adverse events: NSAIDs should be prescribed with extreme caution in patients with a prior history of ulcerative disease or gastrointestinal bleeding. Patients with a prior history of peptic ulcer disease and / or gastrointestinal bleeding who use NSAIDs have a greater than 10-fold increased risk of developing a GI bleed than patients who have neither of these risk factors. Other factors that increase the risk of GI bleeding in patients treated with NSAIDs include concomitant use of oral corticosteroids or anticoagulants, a longer duration of NSAID therapy, smoking, use of alcohol, older age, and poor general health. Most spontaneous reports of fatal GI events are in elderly or debilitated patients and therefore special care should be taken in treating this population.
3. Hypertension: As with all NSAIDs, this drug can lead to the onset of hypertension or the worsening of pre-existing hypertension, either of which may contribute to the increased incidence of cardiovascular events. Patients taking thiazides or loop diuretics may have an impaired response to these therapies when taking NSAIDs. NSAIDs, including this drug, should be used with caution in patients with hypertension. Blood pressure should be monitored closely during the initiation of therapy with this drug and throughout the course of the therapy.
4. Congestive heart failure and edema: Fluid retention and edema have been observed in some patients taking NSAIDs, including this drug. The inhibition of prostaglandin synthesis may lead to worsening of renal function and fluid retention. Therefore, this drug must be administered with caution in patients with heart failure, left ventricular dysfunction, hypertension, edema, or fluid retention. This drug must also be administered with caution in patients on diuretics or patients at risk of blood volume depletion.

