#### Visit 1: Screening visit (Day -14 - Day 1)

At visit 1, the investigator will obtain consent from all subjects and evaluate whether they meet all the inclusion criteria and do not meet any of the exclusion criteria. If deemed suitable for this study, the investigator will conduct the following procedures and evaluations for each subject:

- - Obtain signed consent.
  - Assign screening number.
  - Document demographic data.
  - Document item data.
  - Physical examination (including weight measurement).
  - Vital signs (blood pressure, pulse rate, respiration rate).
  - Take blood sample.
  - Pregnancy test (for women of childbearing potential).
  - Confirm medication history.
  - Check pre-treatment adverse event.
  - Instruct for washout if the subject is on contraindicated medication.
  - (If applies) book visit 2 on Day 1 within 14 days of visit 1.
  - Fill out the case report form.

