#### Visit 2: Randomization visit (Day 1)

Visit 2 will be conducted on Day 1. The investigator will conduct the following procedures and evaluations for each subject:

- - Reconfirm the fulfillment of inclusion / exclusion criteria.
  - Conduct the pain VAS evaluation.
  - Conduct the LDQ evaluation.
  - Randomization.
  - Record all new adverse events and / or changes in pre-existing adverse events.
  - Record all co-administered drugs and / or changes in pre-existing co-administered drugs.
  - Distribute the GSRS and EQ-5D surveys and ask the subjects to answer them.
  - Distribute the investigational products.
  - Explain how to use the ancillary and rescue drugs, and how to fill out the subject log.
  - Distribute the ancillary and rescue drugs.
  - Confirm subject log completion and remind to bring the log at visit 3.
  - Book visit 3: the visit should be 84 days after visit 2 (Day 84 - 87).
  - Fill out the case report form.

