#### Visit 3 (Day 84 - 87)

The following procedures and evaluations will be conducted:

- - Record all new adverse events and / or changes in pre-existing adverse events.
  - Record all co-administered drugs and / or changes in pre-existing co-administered drugs.
  - Conduct the pain VAS evaluation.
  - Conduct the LDQ evaluation.
  - Distribute the GSRS and EQ-5D surveys and ask the subjects to answer them.
  - Physical examination.
  - Vital signs (blood pressure, pulse rate, respiratory rate).
  - Blood sample collection.
  - Collect the unused investigational products, ancillary drugs, and rescue drugs.
  - Collect the completed subject log.
  - Complete the case report form.

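### For subjects taking an NSAID at screening, the only scheduled pre-treatment blood pressure is an on-NSAID value, so the within-arm change in 7.5.3 can understate a rise from the pre-dose state

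*Protocol*

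**What the plan says.** The Synopsis sets "Vital signs (VS): at V1 and V3". The visit lists in Protocol section 6.1 agree with it: blood pressure, pulse and respiration appear at Visit 1 and Visit 3 and are absent from Visit 2. Visit 1 also carries the step "Instruct for washout if the subject is on contraindicated medication", and Visit 2 is to be booked no more than 14 days later.

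Section 5.3.2, item 1, bars "NSAIDs (LDA [≤325 mg / day low dose aspirin] excluded) within 7 days prior to administration of the investigational product". Other drugs are on the same list, for example "Gastroprotective agents (including H2 blockers, PPIs, misoprostol, etc.) within 7 days prior to administration of the investigational product". Appendix 1, footnote 1, allows screening and randomization on the same day only when no further washout is needed.

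Section 7.3.2 lists vital signs after 12 weeks among the secondary endpoints. Section 7.5.3 describes them before and after treatment, tests the change within each arm with a paired t-test or Wilcoxon signed rank test, and compares the arms with a two-sample test. On the pharmacology, the general precautions for the control drug (section 5.3.5.4) state: "As with all NSAIDs, this drug can lead to the onset of hypertension or the worsening of pre-existing hypertension".

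**The concern.** A before/after comparison of blood pressure is most useful when the first value reflects the state just before the study drug starts. Here the first value may have been taken under another NSAID, a class that the protocol itself says can raise blood pressure. If part of that effect has gone by Day 1, the change from Visit 1 to Visit 3 is smaller than the change from the pre-dose state to Visit 3.

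Both arms contain an NSAID and there is no placebo arm (section 4.1, Control group). A rise common to both arms therefore cannot show in the between-arm test, and the within-arm change is the only planned vital-sign analysis that could show it. The affected subgroup is foreseeable, since section 2.5 describes the subjects as osteoarthritis patients who need NSAID therapy, but its size is not given. A Day 1 value that was never measured cannot be recovered at the analysis stage.

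**Working it through.** **Who is affected.** The protocol gives no figure for this point, so the first step is to set the schedule out.

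| Subject at Visit 1 | Visit 1 to first dose | State at the only scheduled pre-treatment reading |
| --- | --- | --- |
| On an NSAID other than low-dose aspirin | at least 7 days (5.3.2, item 1), at most about 14 (6.1, Visit 1) | on the earlier NSAID |
| Washing out another listed drug only | up to about 14 days | not on an NSAID; outside this point |
| No washout, Visits 1 and 2 both on Day 1 | 0 days | pre-dose state; outside this point |

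**Bias in the within-arm change.** Let V1, V2 and V3 be a subject's blood pressure at the three visits, with V2 the unscheduled pre-dose value. Then

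V3 − V1 = (V3 − V2) − (V1 − V2).

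Let f be the share of the arm on an NSAID (other than low-dose aspirin) at Visit 1, and d the mean of V1 − V2 in those subjects. Take V1 − V2 to average zero in everyone else. Averaging over the arm:

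mean(V3 − V1) = mean(V3 − V2) − f × d.

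The planned within-arm change understates the change from the pre-dose state by f × d when d is positive. It is correct when d is zero and overstates when d is negative.

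**Size.** Neither f nor d is in the protocol. All values below are assumptions, and the results are in mmHg.

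| | d = 0 | d = 2 | d = 5 |
| --- | --- | --- | --- |
| f = 0.25 | 0 | 0.25 × 2 = 0.50 | 0.25 × 5 = 1.25 |
| f = 0.50 | 0 | 0.50 × 2 = 1.00 | 0.50 × 5 = 2.50 |
| f = 0.75 | 0 | 0.75 × 2 = 1.50 | 0.75 × 5 = 3.75 |

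**Between-arm comparison.** Visit 1 precedes randomization, so f and d have the same expectation in both arms and f × d cancels in the difference of changes. There is no bias in expectation.

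**Number of extra readings.** With 53 subjects per arm, a Visit 2 reading for everyone screened on an earlier day is at most 2 × 53 = 106.

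**The case against.** The case against is substantial, and much of it stands.

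- **The schedule is consistent, and the safety objective is comparative.** The Synopsis, the visit lists and section 7.5.3 do not contradict one another, and the stated purpose is to compare overall safety between the drugs. Without a placebo arm the within-arm change is descriptive under either baseline. Change from the usual treated state also has meaning in patients who need an NSAID. This limits the importance of the point. It does not change what the planned paired test compares for the affected subjects.
- **The size is unsupported by the protocol, and so is the sign.** Visit 2 follows NSAID withdrawal and requires a pain VAS of at least 40 mm, so Visit 1 minus Visit 2 blood pressure could be small or even negative. That stands. A reader might infer a large loss of power in the paired test, but this would need a value for f, a d equal to the study drug's own effect with full offset by Day 1, and a standard deviation of the change. None of these is in the protocol.
- **Other safety capture exists.** Adverse events are recorded at every visit, clinically significant abnormal measurements that arise or worsen count as adverse events (section 6.3.1), and additional visits may include vital signs. Overt hypertension may therefore still be seen; a modest mean shift would not be.
- **Laboratory values share the Visit 1 and Visit 3 schedule.** That is true, and similar reasoning could be applied to them. It does not weaken the point for blood pressure, where the remedy needs no blood draw.

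Two stronger readings are tempting. First, a reader might contrast vital signs with the LDQ, since the Visit 2 list includes "Conduct the LDQ evaluation". But every LDQ symptom item in Appendix 2 asks about the last four weeks, longer than the screening period, so the Visit 2 LDQ is not a clean post-washout baseline either. Only the pain VAS is confined to Visit 2 rather than Visit 1 at baseline (Appendix 1, footnote 5). Second, the control-drug precautions add "Blood pressure should be monitored closely during the initiation of therapy with this drug and throughout the course of the therapy". One pre-dose reading supplies a reference value; it is not that monitoring.

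**Conclusion.** The point holds in a limited form. It covers only subjects taking an NSAID other than low-dose aspirin at Visit 1, only scheduled readings, and only the within-arm vital-sign change. For them the baseline is an on-NSAID value, and the arm's mean blood pressure rise from the pre-dose state can be understated by f × d. That is 0.5 to 3.75 mmHg if f is 0.25 to 0.75 and d is 2 to 5 mmHg, and nil if either is zero. These ranges are assumptions, as is a positive d, and the point does not require blood pressure to be fully drug-free by Day 1.

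A reader might go further and infer that the safety comparison of the two drugs, or the non-inferiority result, is compromised. The protocol does not support this: the term cancels in expectation between randomized arms, and the LDQ analysis does not use vital signs. This is a minor improvement to a descriptive secondary safety summary, worth considering because it is cheap and cannot be made after dosing has begun.

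**What to change.** Add blood pressure, pulse and respiration before the first dose at Visit 2 for every subject whose Visit 1 is not on Day 1. Put this in the Visit 2 list of section 6.1, in the vital-signs line of the Synopsis and in the vital-signs row of Appendix 1. In section 7.5.3, define the vital-sign baseline as the last value before the first dose, and keep the Visit 1 reading for screening.

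The cost is one set of readings and one case report form entry per such subject, at a visit that already takes place. It includes subjects with separate visit dates who did not need washout, because one rule for all is simpler than a rule tied to earlier drug use. The change adds no monitoring between Day 1 and Day 84 and does not affect the sample size.

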| Exclusion criteria | 1. Persons who are participating in a clinical study or have participated in a clinical study <30 days prior (participation is based on the date of final investigational product administration). 2. Persons with a history of abuse of alcohol or other drugs <6 months prior to screening. 3. Persons who drink 21 standard drinks or more per week (generally, 55 mL soju is equated to 200 mL beer or 30 mL spirits). 4. Persons with a history of peptic ulcer disease with complications (bleeding, perforation, penetration, and gastric outlet obstruction) within the last 5 years. 5. Persons with a history of peptic ulcer disease without complications within 6 months prior to screening visit or persons with active peptic ulcer disease. 6. Persons who have been infected with *Helicobacter* but did not undergo eradication therapy. 7. Persons with a known history of gastroesophageal reflux disease. 8. Persons with a confirmed diagnosis or clinical suspicion of the following arthropathies that may affect safety and efficacy evaluation: septic arthritis, inflammatory arthropathy such as rheumatoid arthritis, gout, recurrent pseudopain, Paget’s disease, fracture, ochronosis, acromegaly, hemochromatosis, Wilson’s disease, primary osteomalacia, and Ehlers Danlos Syndrome and other genetic collagen disorders. 9. Persons with surgery planned during the study period. 10. Persons with a history of gastrointestinal cancer. 11. Persons with a GI disorder due to drug absorption malfunction. 12. Persons with gastrointestinal bleeding, cerebrovascular bleeding, other bleeding disorders, or severe hematological disorders. 13. Persons with moderate to severe hepatic impairment (Child Pugh Class II or higher). 14. Persons with a history of severe heart failure or coronary artery bypass graft (CABG). 15. Persons with severe renal impairment (CrCl <30 mL / min). 16. Persons with severe hypertension (SBP ≥160 mmHg or DBP ≥100 mmHg) refractory to treatment. 17. Persons with a history of allergy to components of the investigational product. 18. Persons with hypersensitivity or allergy to other NSAIDs or PPI. 19. Subjects who received a contraindicated drug or therapy within a pre-specified period prior to study participation (Section 5.3.2). 20. Patients who are receiving a contraindicated co-administration drug (Section 5.3.3). 21. Patients who have a history of surgery on the osteoarthritic joint within the past year. 22. Women who are pregnant or breastfeeding, or women of childbearing age who are not using appropriate contraception (condom, diaphragm, intrauterine contraceptive device, or hormonal contraceptive drug used from ≥21 days prior to investigational product administration, or male vasectomy); this clause does not apply to menopausal women. 23. Persons deemed inappropriate for study enrollment by the investigator due to clinically relevant medical or psychiatric conditions. |

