## Discussion of the risk-benefit of the administration of the investigational product

This study is a phase 4 clinical study on osteoarthritis patients requiring NSAID administration.

The investigational product, the Naxozol tablet, is a slow-release tablet that contains naproxen, an NSAID, and esomeprazole, a PPI.

The clinical efficacy of NSAIDs in pain control in osteoarthritis patients is well accepted. Naproxen, an NSAID, and esomeprazole, a PPI, are both widely used and are safe drugs for pain improvement in osteoarthritis patients and for treatment of gastrointestinal bleeding or symptoms of dyspepsia associated with NSAID use, respectively.

The American College of Gastroenterology (ACG) guideline also recommends co-administration of PPI with NSAID use in patients with a moderate risk of gastrointestinal bleeding. (10)

Furthermore, in conducting this study, the contraindications for the investigational product have already been reflected in the inclusion / exclusion criteria, ensuring exclusion of high risk groups from the study.

In conclusion, a 12-week administration of Naxozol to osteoarthritis patients would not greatly increase the risk of harm to subjects if preceded by appropriate subject selection and followed-up by monitoring of adverse events. The safety of a 12-week oral administration within the given dose range is expected to be satisfactory with careful monitoring of adverse events and vital signs.

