## Inclusion criteria

- 1. Subjects of Korean nationality who voluntarily decide to participate in the study and provide written consent after receiving and understanding a detailed description and explanation of the study.
  2. Men and women aged 50 years or older at the time of consent.
  3. Persons who are available for follow-up throughout the study duration and are able to perform due tasks for the study, such as reading and filling out EQ-5D and VAS surveys.
  4. Persons with a confirmed medical history of physically symptomatic osteoarthritis who score 40 mm or greater on the pain VAS performed at V2.
  5. Persons deemed appropriate for the study based on the screening results (NB: subjects can be included at the discretion of the investigator even if laboratory test results are outside the reference ranges).

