22. Women who are pregnant or breastfeeding, or women of childbearing age who are not using appropriate contraception (condom, diaphragm, intrauterine contraceptive device, or hormonal contraceptive drug, used from 21 days prior to investigational product administration, at least, or male vasectomy); this clause does not apply to menopausal women.
23. Persons deemed inappropriate for study enrollment by the investigator due to clinically relevant medical or psychiatric conditions.
    1. **Subject allocation/investigational product administration**

Subjects who meet the inclusion / exclusion criteria and have given written consent before study participation will be randomly allocated to each study group to receive the investigational products (refer to Section 7.2).

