## Contraindications for the experimental drug

The following are contraindications for this drug:

1. Known hypersensitivity to naproxen, esomeprazole, any component of this drug, or substituted benzimidazoles.
2. A history of asthma, rhinitis, nasal polyps, urticaria, or other allergic-type reactions after taking aspirin or other NSAIDs, including COX-2 inhibitors (fatal and severe anaphylactic reaction has rarely been reported in such patients after NSAID use).
3. Active peptic ulcer disease.
4. Gastrointestinal bleeding, cerebrovascular bleeding, other bleeding disorders, or a severe hematological disorder.
5. Severe hepatic dysfunction (e.g. Child-Pugh class C).
6. Severe cardiac failure.
7. Severe renal failure (CrCl <30 mL / min).
8. Severe hypertension.
9. Use during the peri-operative period of coronary artery bypass graft (CABG) surgery.
10. Use during the last 3 months of pregnancy.
11. Atazanavir or nelfinavir use.

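### Exclusion 16 removes severe hypertension only when it is refractory to treatment, although the protocol contraindicates Naxozol in severe hypertension without condition

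*Protocol*

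**What the plan says.** Exclusion 16 appears in the same words in the Synopsis and in Section 4.3.2: "Persons with severe hypertension (SBP ≥160 mmHg or DBP ≥100 mmHg) refractory to treatment". It is the only eligibility criterion that mentions blood pressure.

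Section 5.3.4.2 (contraindications for the experimental drug) lists at item 8 "Severe hypertension", with neither a threshold nor a condition. Section 5.3.4.4 separately lists hypertension in general among the states that call for caution, so the protocol treats the severe form differently from the rest.

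Section 2.9 says that "the contraindications for the investigational product have already been reflected in the inclusion / exclusion criteria" and bases its risk-benefit conclusion partly on that.

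Two discretionary clauses could also apply. Inclusion 5 admits "Persons deemed appropriate for the study based on the screening results", and exclusion 23 removes "Persons deemed inappropriate for study enrollment by the investigator due to clinically relevant medical or psychiatric conditions". Neither gives a blood-pressure limit.

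On monitoring, the Synopsis schedules "Vital signs (VS): at V1 and V3". The general precautions for the control drug (Section 5.3.5.4, item 3) state: "As with all NSAIDs, this drug can lead to the onset of hypertension or the worsening of pre-existing hypertension". The same item asks for close blood-pressure monitoring when therapy starts and throughout its course.

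**The concern.** The criterion sets a numerical definition of severe hypertension and then adds a second requirement, that treatment has failed. A person who has never been treated, or whose hypertension is first detected at screening, cannot satisfy that requirement. A person above the limit on a first antihypertensive arguably does not satisfy it either. The protocol does not define refractory by number of drugs or by duration, so the 10 sites may apply it differently.

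The result is that a candidate with a condition the protocol itself lists as a contraindication to Naxozol can pass every mandatory criterion. What is at stake is subject safety and the accuracy of the Section 2.9 statement. The estimate of the treatment effect is not at stake.

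**Working it through.** No figure in the plan is in dispute on this point. The check is a comparison of texts plus one interval calculation.

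**1. Contraindications in Section 5.3.4.2 against the exclusions in Section 4.3.2**

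| Contraindication | Exclusion | How it is carried over |
| --- | --- | --- |
| Item 4, bleeding and severe haematological disorders | 12 | Essentially unchanged |
| Item 5, severe hepatic dysfunction | 13 | Widened to moderate impairment |
| Item 6, severe cardiac failure | 14 | Widened to a history of it |
| Item 7, renal failure, CrCl <30 mL/min | 15 | Same limit |
| Item 8, severe hypertension | 16 | Narrowed to cases refractory to treatment |

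Items 4 to 7 are carried over at equal or greater breadth. Item 8 is narrowed, and the protocol gives no reason.

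**2. A worked candidate**

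Take an untreated candidate at 180/110 mmHg at V1.

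- Threshold in exclusion 16: 180 ≥ 160 and 110 ≥ 100, so it is met.
- Treatment condition in exclusion 16: there has been no treatment to fail, so it is not met. Exclusion 16 does not apply.
- Other exclusions: none mentions blood pressure. Exclusions 19 and 20 concern prior and concomitant drugs or therapies.
- Inclusion 5 and exclusion 23: left to the investigator's judgement.

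The candidate may be randomised.

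**3. Whether later steps close the gap**

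- At V2 the criteria are reconfirmed (Section 6.1), but no vital signs are taken and the same criterion is applied again.
- The first stopping trigger in Section 4.5.2 is fulfilment of an exclusion criterion, so it inherits the gap.
- Under Section 6.3.1.1 a pre-existing condition that does not worsen is not an adverse event, so baseline severe hypertension does not by itself prompt an additional visit.
- Section 1.4 states that no data safety monitoring committee is appointed.

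**4. Time between scheduled blood-pressure readings**

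Inputs: V1 to V2 is 0 to 14 days (Synopsis; Section 6.1). V3 is Day 84 ± 7 from randomisation (Synopsis).

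- V2 to V3: 84 − 7 = 77 days to 84 + 7 = 91 days.
- V1 to V3: 77 + 0 = 77 days to 91 + 14 = 105 days.

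Section 6.1 and Appendix 1 give a narrower V3 window of Day 84 to 87. Counting those as days from V2, the V1 to V3 gap is 84 + 0 = 84 days to 87 + 14 = 101 days. On either window, about 12 weeks of dosing pass without a scheduled reading.

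**The case against.** The strongest reply is that Section 5.3.4.2 gives no definition of severe hypertension. Exclusion 16 could then be read as the protocol's own working form of that contraindication, with treatment failure as part of it, and Section 2.9 would not be contradicted. The absence of a number in Section 5.3.4.2 is a fair point. But exclusion 16 attaches its limits to the term severe hypertension and then adds the refractory condition as something further, and nothing in Section 5.3.4.2 makes severity depend on response to treatment.

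A second reply is that the investigator has safeguards. Section 4.1 refers the reader to Section 5.3 and asks for careful review of eligibility and health status, and inclusion 5, exclusion 23 and the V2 reconfirmation are all available. Many investigators would turn such a patient away. That lowers the practical risk, but each of these either relies on judgement or reapplies the same criterion.

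Third, severe hypertension is not the only imperfect carry-over. Nelfinavir is contraindicated with Naxozol in Section 5.3.4.2, while Sections 5.3.2 and 5.3.3 name only atazanavir among the antiretrovirals. Several celecoxib contraindications in Section 5.3.5.2, such as inflammatory bowel disease, have no specific exclusion. This stands: correcting exclusion 16 makes Section 2.9 accurate on blood pressure only. It does not defend the wording of exclusion 16.

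Finally, the interval between readings describes the schedule for every subject and does not measure the effect of this wording. That is correct. It shows only why the screening criterion has to do the work.

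**Conclusion.** The concern holds. As written, exclusion 16 does not cover untreated severe hypertension, the protocol contraindicates Naxozol in severe hypertension without condition, and Section 2.9 states that the contraindications are covered. This should be corrected.

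The conclusion rests on one assumption: that severe hypertension in Section 5.3.4.2 means SBP ≥160 or DBP ≥100 mmHg, which is the only definition the protocol gives. The celecoxib contraindications in Section 5.3.5.2 do not name hypertension, so the conflict concerns Naxozol; but any candidate may be allocated to Naxozol, so eligibility has to respect its contraindications for everyone.

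The number of subjects affected cannot be derived from the documents. For any such subject, 77 to 91 days after randomisation would pass before the next scheduled blood pressure under the Synopsis window, unless an adverse event led to an additional visit. The margin, the sample size and the primary analysis are unaffected.

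**What to change.** Delete the last three words of exclusion 16 in the Synopsis and in Section 4.3.2, and tie the limit to the screening reading: SBP ≥160 mmHg or DBP ≥100 mmHg at screening excludes the patient, treated or untreated. Section 5.3.4.2 can then stand unchanged, and Section 2.9 becomes correct on this point.

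The cost is a wording amendment to one criterion in two places. No new procedure is needed, because blood pressure is already measured at V1. Some candidates will be screened out, a number the documents do not give. If the sponsor does not want to exclude on a single reading, a rule for a confirmatory repeat at screening could be added, at the price of that extra measurement.
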